## Abstract

**Background:**

The World Health Organization (WHO) recommends seasonal malaria chemoprevention (SMC) with sulfadoxine-pyrimethamine and amodiaquine (SPAQ) for children aged 3 to 59 months, living in areas where malaria transmission is highly seasonal. However, due to widespread prevalence of resistance markers, SMC has not been implemented at scale in East and Southern Africa. An initial study in Uganda showed that SMC with SPAQ was feasible, acceptable, and protective against malaria in eligible children in Karamoja region. Nonetheless, exploration of alternative regimens is warranted since parasite resistance threats persist.

**Objective:**

The study aims to test the effectiveness of SMC with Dihydroartemisinin-piperaquine (DP) or SPAQ (DP-SMC & SPAQ-SMC), chemoprevention efficacy as well as the safety and tolerability of DP compared to that of SPAQ among 3-59 months old children in Karamoja region, an area of Uganda where malaria transmission is highly seasonal.

**Methods:**

A Type II hybrid effectiveness-implementation study design consisting of four components: 1) a cluster randomized controlled trial (cRCT) using passive surveillance to establish confirmed malaria cases in children using both SPAQ and DP; 2a) a prospective cohort study to determine the chemoprevention efficacy of SPAQ and DP (if SPAQ or DP clears sub-patent infection and provides 28 days of protection from new infection) and whether drug concentrations and/or resistance influence the ability to clear and prevent infection; 2b) a sub study examining pharmacokinetics of DP in children between 3 to <6 months; 3) a resistance markers study in children 3–59 months in the research districts plus the standard intervention districts to measure changes in resistance marker prevalence over time and finally; 4) a process evaluation.

**Discussion:**

This study evaluates the effects of SPAQ-SMC versus DP-SMC on clinical malaria in vulnerable children in the context of high parasite SP resistance, whilst informing on the best implementation strategies.

**Conclusion:**

This study will inform malaria policy in high-burden countries, specifically on utility of SMC outside the sahel, and contribute to progress in malaria control.

## Introduction

Seasonal malaria chemoprevention (SMC) is a very potent community-based intervention to avert malaria infections due to Plasmodium falciparum in areas such as the Sahel region, where malaria morbidity and mortality are high and malaria transmission is seasonal
^
1–
3
^. It entails the intermittent administration of antimalarials to at-risk populations during the period of greatest risk: usually coinciding with the rainy season. Since 2012, SMC has been recommended for children aged 3-59 months using sulfadoxine-pyrimethamine (SP) and amodiaquine by the World Health Organization (WHO)
^
4
^. Owing to concerns over widespread parasite resistance to SP and AQ across east and southern Africa, the Sahel region of west and central Africa has historically been prioritised for the scale-up of SMC. In 2020, SMC was implemented in 13 Sahelian countries targeting over 33 million children
^
5
^. Consolidated guidelines for malaria published by WHO in 2023 no longer provide specific parameters for the deployment of SMC in terms of seasonality, drug regimen or therapeutic efficacy of the antimalarials used, emphasising the importance of context and local evidence
^
6
^.

There is therefore a need to explore if SMC can be a viable malaria prevention strategy in new geographies, including those where resistance to SP and AQ is high, especially since the definition is not clear regarding the relation between resistance and the effectiveness of SMC. Studies have shown that across east and southern Africa P falciparum responses to SP are seriously compromised
^
7–
9
^, and SP is no longer recommended for treatment of malaria episodes. Several mutant alleles that confer parasite resistance to SP are commonly found in the region, including in P falciparum dihydrofolate reductase (pfdhfr) gene at codons 51, 59 and 108, and in P falciparum dihydropteroate synthase (pfdhps) gene at codons 437 and 540
^
10
^. The combination of three mutations in pfdhfr (51I, 59R, and 108N) and two in pfdhps (437G and 540E) leads to an intermediate level of SP resistance
^
11
^. Addition of either pfdhfr164L or pfdhps 581G leads to higher-level SP resistance
^
11
^. These additional mutations have been rare in Africa, but some reports have noted moderate prevalence of the pfdhfr 164L mutation in parasites from south-western Uganda
^
12–
15
^, and of the pfdhps581G mutation in parasites from Uganda and Tanzania
^
8,
9,
16
^. For another malaria chemoprevention strategy, intermittent preventive treatment in pregnancy (IPTp), which also uses SP, it has been suggested that parasite resistance may undermine the effectiveness of the intervention
^
17
^. Markers associated with amodiaquine resistance have also been found, including in the P falciparum multidrug resistance 1 (Pfmdr1) gene and the chloroquine resistance transporter (PfCRT). Even if the effectiveness of SMC in the context of high parasite existence can be demonstrated, it will also be important to identify alternative SMC drug regimens that could replace SPAQ in the future.

The Uganda National Malaria Reduction Strategic Plan 2021-2025 recommends the implementation of SMC in areas with highly seasonal malaria to accelerate progress towards malaria elimination
^
18
^. In response to this recommendation, the National Malaria Control Division (NMCD) and Malaria Consortium are conducting SMC implementation research in Karamoja subregion. In 2021, SMC using SPAQ was implemented in two districts with a combined target population of 85,000 children 3–59 months. Five monthly SMC cycles were implemented between May and September. Village Health Teams, a recognised cadre of community health workers, served as community distributors, with supervision provided by health facility-based health workers. The intervention was found to be feasible and acceptable, with high coverage achieved through the standard door-to-door delivery mechanism. There were also indications that the intervention was effective in preventing malaria cases among targeted children. However, there remains a need to generate robust evidence of effectiveness using appropriate study designs. There is also a need to further explore if SMC using SPAQ can provide a sustained, prolonged protective effect against malaria in the context of parasite resistance.

In 2022, SMC will be implemented in eight districts of Karamoja, targeting 270,000 children 3–59 months. As in the previous year, five monthly SMC cycles will be implemented using a door-to-door delivery model. The majority of children will receive SMC with SPAQ, while around 15,000 children will receive SMC with dihydroartemisinin-piperaquine (DP). As there is currently no age-based dosing regimen for SMC, DP will be given according to a weight-based dosing regimen. In Uganda, DP is used as second-line treatment for uncomplicated malaria and remains highly effective and safe for the treatment of uncomplicated malaria
^
19,
20
^. It has also been used successfully in mass drug administration and to reduce malaria incidence in emergency settings. DP could be an alternative SMC drug regimen primarily due to its long half-life. However, there is insufficient evidence of its tolerability in very young children as safety studies have typically involved only children above 6 months.

## Protocol

### Aims and objectives

This study phase aims to test the feasibility, effectiveness, and chemoprevention efficacy of SMC with SPAQ and DP in Karamoja region in Uganda, where malaria transmission is highly seasonal, and inform malaria policy in Uganda. Specific objectives include: 1) to determine the effectiveness of SMC with SPAQ and DP in terms of its reduction in incidence of malaria infection among children aged 3–59 month for SPAQ and children 6–59 months for DP; 2a) to conduct a prospective chemoprevention efficacy cohort study to determine if SPAQ and DP clear existing parasitemia and provide 28 days of protection from infection and whether drug concentrations and/or SPAQ or DP drug resistance influence the protection duration of these two SMC regimen; 2b) to assess the safety of DP in children 3–6 months through pharmacometric analysis; 3) to conduct a resistance markers study in children 3–59 months in the two research districts plus the three standard intervention districts to measure changes in resistance marker prevalence over time; and 4) to assess the impact of the SMC implementation model, determining process, costing and acceptability outcomes for the intervention.

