### Population

Eligible participants for receiving SMC will be male or female children with no fever, aged 3–59 months for any of the SMC cycles, staying in the districts of Kotido, Moroto and Nabilatuk districts (where delivery is continuing from Phase 1 and where coverage surveys will be conducted in Phase 2), and randomly-selected areas in Amudat and Nakapiripirit.

Additionally, other key stakeholders who will be sampled include health workers participating in implementing SMC, health officials at different levels of the health system, community leaders, and caregivers of children below ten years of age, (see
Table 1 for estimated population sizes).

**Table 1. T1:** Sample sizes for each objective.

Objective	Study population	Estimated sample size
1	cRCT: Sample of eligible children in Amudat district of age 3–59 months, resident in the study area for at least a month, planned for DP and SPAQ	4,270
2a	Chemoprevention efficacy cohort study – children under 3–59 months for SPAQ and 6-59 months for DP	1,250
2b	Safety of DP in 3–6 month old children through pharmacometrics to low dose DP.	30
3	Resistance Marker study – children under 5	1,500
4	Assessment of the SMC implementation model, deciding the process, costing and acceptability outcomes of the intervention	144
**Total number of participants:**		**7,194**

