### Eligibility criteria

Inclusion and exclusion criteria for each objective are detailed in
Table 2 below.

**Table 2. T2:** Eligibility Criteria.

Inclusion criterion	(1)	(2)	(3)	(4)
Children between 3–59 months	x	x	x	
Being resident in the study area	x	x	x	
Afebrile with no other malaria associated symptoms in the past 48 hours or at time of recruitment	X	X		
Consent to participate in the study obtained	X	X	X	
Willingness and ability of the child’s guardians to comply with the study protocol for the duration of the study including attending a designated health centre if their child has malaria symptoms during the data collection period	x	X		
Can comply with 3 days DOT of standard SPAQ or DP regimen (day 0–2		x		
Clinical signs and symptoms suggestive of malaria infection: fever (axillary temperature ≥37.5ºC) or history of fever in the preceding 24 hours.			X	
Positive RDT			x	
A person aged 18 years or older with primary or caring responsibility for the feeding and daily care of at least one child aged 3–59 months, who has been resident in Nabilatuk, Kotido, Moroto, Amudat or Nakapiripirit prior to the beginning of the SMC pilot				x
Community members, community leaders, religious leaders				X
Village Health Teams (VHTs) involved in the distribution of SMC in Nabitatuk, Kotido, Moroto, Amudat and Nakapiripirit				X
Community Health Workers, Community Distributors				X
District level health officials (District Health Officers, Malaria Focal Persons)				X
Provincial level health officials				X
Implementing partners				X
National level policy makers				X
Gender experts and/or gender advocates				x
Exclusion criterion	(1)	(2)	(3)	(4)
Malaria symptoms (tympanic fever ≥ 37.5°C or history of fever in past 48 hours)	X	X		
Known allergy to medicine provided	X	X		
Receiving a sulfa-based medication for treatment or prophylaxis, including co-trimoxazole (trimethoprim– sulfamethoxazole)	X	X		
Individuals receiving azithromycin due to the antimalarial activity of azithromycin	X	x		
Severe malnutrition according to WHO guidelines	X	X		
Recruited in any other SMC study element	X	X		
Children with HIV or ARV use	X	X		
Children with a history of severe adverse reaction to SP, AQ or DP or have used SP within the previous month before recruitment	x	X		
Treatment of uncomplicated malaria with DP in the past 28 days		X		
Chronic illness of any kind		X		
Recruited in cRCT or any other studies		X		
Treatment with an ACT in previous 2 weeks		X		

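### Objective 1 defines the cRCT on 3–59 months for SPAQ but 6–59 months for DP, while Table 1's cRCT row, Table 2 and the abstract give a single 3–59 month range, so the DP contrasts lack a stated common age range

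*Protocol article*

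**What the plan says.** The protocol article gives the age range of the DP group in several places.

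- **Aims and objectives, objective 1 (cRCT):** the effect is defined as "reduction in incidence of malaria infection among children aged 3–59 month for SPAQ and children 6–59 months for DP".
- **Table 1, objective 1 (cRCT):** one range covers both drugs, namely children "of age 3–59 months, resident in the study area for at least a month, planned for DP and SPAQ".
- **Table 2, age criterion:** "Children between 3–59 months" is ticked for components 1, 2 and 3, with no separate limit for DP.
- **Population:** children are eligible for SMC if "aged 3–59 months for any of the SMC cycles", again with no split by drug.
- **Abstract, Objective:** the aim includes "safety and tolerability of DP compared to that of SPAQ among 3-59 months old children".
- **Table 1, objective 2a (cohort):** "children under 3–59 months for SPAQ and 6-59 months for DP", which agrees with the split in objective 1.

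DP in the youngest infants is also the subject of a separate sub-study, 2b, with 30 children. The abstract's Discussion names SPAQ-SMC versus DP-SMC as what the study evaluates. Recruitment and data collection names a Cox model for the cRCT, without an age restriction or covariates.

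**The concern.** The objective and the eligibility statements for the same cRCT describe different DP populations, and each reading causes a problem.

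If objective 1 governs, the SPAQ arm (and the control arm, through Table 2) includes children of 3–5 months and the DP arm does not. The arms then differ in age by design, and randomising clusters does not remove that difference.

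If the tables govern, the arms match in age, but the DP clusters contain enrolled children outside the population for which objective 1 defines the DP effect.

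Exposure, immunity and care seeking can all vary with age in early childhood. The DP–SPAQ contrast is a main interest of the study, and the true difference between two active regimens may be small, so even a modest systematic shift is worth removing. A larger sample would not shrink it.

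**Working it through.** **Plan's own figure.** The Table 1 rows add up: 4,270 + 1,250 + 30 + 1,500 + 144 = 7,194, as stated. The article gives no event rate, arm split or age structure, so the size of the age mismatch can only be bounded under assumptions.

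**Can sub-study 2b explain the single range?** Column 2 of Table 2 is not divided into 2a and 2b, and 2b does enrol infants on DP, so 3–59 months may be a fair outer range for that column. Column 1 of Table 2 and the objective 1 row of Table 1 concern the cRCT only, and 2b cannot explain those.

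**Share of children affected (assumption: uniform ages).** The range 3–59 completed months has 57 monthly ages, of which 3, 4 and 5 make three.

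- s = 3/57 = 0.0526, or 5.3%.
- 0.0526 × 4,270 ≈ 225 cRCT children in the whole trial.
- With three equal arms (split not stated), 225/3 ≈ 75 per arm.

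**Shift in the ratio if objective 1 governs.** Let r be the incidence at 3–5 months relative to 6–59 months in the comparator arm. Set incidence at 6–59 months to 1 and let the two drugs be equally effective. The DP group (6–59 months) has incidence 1, and the SPAQ group (3–59 months) has (1 − s) + s·r. The apparent DP/SPAQ ratio is therefore 1 / [(1 − s) + s·r].

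| r (assumed) | Denominator at s = 0.0526 | Apparent DP/SPAQ ratio |
|---|---|---|
| 0 | 0.9474 | 1.056 |
| 0.25 | 0.9605 | 1.041 |
| 0.5 | 0.9737 | 1.027 |
| 1 | 1.0000 | 1.000 |
| 1.5 | 1.0263 | 0.974 |

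If s is varied from 3% to 8%, with r from 0 to 1.5, the extremes are 0.962 and 1.087 (both at s = 8%). The same factor would multiply a true DP/control ratio if control children are enrolled from 3 months.

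**The case against.** The strongest reply is that the single ranges are outer limits. Table 2's columns are components rather than arms, the cRCT row of Table 1 pools all arms, and the abstract's objective spans the whole study including 2b. On this view the DP limit in objective 1 simply is not repeated everywhere. Objective 1 also does not say that DP at 6–59 months will be set against SPAQ or control at 3–59 months. The full protocol or the SAP, neither of which is shown, may restrict or adjust for age.

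Much of this stands. It explains column 2 of Table 2, makes the abstract weaker evidence, and rules out a claim that infants of 3–5 months were enrolled in DP clusters. It does not settle the point. If the pooled ranges are only outer limits, the cRCT arms have different age ranges, and the article states no common one for the contrast it says it evaluates. An SAP can add covariates, but the population in the objective and the eligibility criteria belong to the protocol, and here they conflict.

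For cohort 2a the article specifies no explicit DP–SPAQ test and recruitment is non-randomised, so age would be only one of several threats to such a comparison.

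**Conclusion.** The inconsistency for the cRCT is real, and as written the DP contrasts are not on a common age range. Any DP–SPAQ comparison in cohort 2a shares the problem, because its row in Table 1 states the split outright. The likely bias is small: a ratio of about 0.97 to 1.06 at a 5.3% share, and 0.96 to 1.09 over shares of 3% to 8%. It vanishes at equal incidence and its direction is unknown. These figures rest on an assumed age distribution and assumed relative incidence, since the article gives neither.

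Three stronger inferences are tempting and not supported.

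- *Both tables admit 3–59 months for DP throughout.* The 2a row of Table 1 says otherwise.
- *Every comparison involving DP mixes drug with age.* A contrast limited to 6–59 months, or adjusted for age, would avoid or reduce this, and the SAP that might specify it is not shown.
- *Untreated infants counted in the DP arm would inflate the DP/control ratio by 12%.* This takes a true ratio of 0.30 to 0.9474 × 0.30 + 0.0526 = 0.337, and it requires infant incidence equal to that of older children. With relative incidence ρ of 0.3 to 0.7, (0.9474 × 0.30 + 0.0526ρ)/(0.9474 + 0.0526ρ) gives 0.311 to 0.326, about 4% to 9%. The article states neither the 0.30 nor that such children went untreated.

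**What to change.** Reconcile the abstract's objective, objective 1, the Population section, Table 1 and Table 2 so that they state the same ages for the DP group in each component. Which range is right is for the investigators to state, and this review does not choose one. Since Study status reports data collection complete, the text should describe the rule that was actually applied.

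Then define every contrast involving DP, in the cRCT and in cohort 2a, on the age range at enrolment that is common to the compared arms, with the same restriction in each arm. Using age at enrolment keeps the analysis set fixed when infants grow older during the five cycles. Keep 3–59 months for SPAQ versus control.

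The cost is a correction of wording and one line defining the analysis population. Age is already needed to establish eligibility, so no new data are required. If the common range starts at 6 months, about 5% of SPAQ and control children (under uniform ages) drop out of the DP contrasts, with a correspondingly small loss of precision.

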** Children will be screened at the community level by research assistants with the help of VHTs and referred to a designated study clinic for further assessment and non-randomized recruitment. At the study clinic, study clinicians will confirm eligibility criteria through conversation with the caretaker and obtain informed consent. Enrolled children will receive SMC via directly observed therapy (DOT) over the first three days and will have malaria thick smears and dry blood spots (DBS) taken at day 0, 2, 7, 14, 21 and 28 throughout and after administering a single cycle of SPAQ or DP. In addition, the study clinician will assess if the child received other treatment or experienced any problem during all the scheduled sample collection days (Day 0, 7, 14, 21, 28) as well as bed net usage. Caregivers and guardians will also be reminded at each visit to seek care at a health facility or from a community health worker if the child becomes febrile. Children who become febrile and are confirmed on HPR2-pLDH RDT between day 0 and day 28 will have an additional DBS taken and then treated using standard guidelines. All DBS samples will be processed for all of the SMC drugs on days 7 and for sulfadoxine, amodiaquine and piperaquine for day 28. Individual surveys on day 28 after the final DBS is taken will be conducted to determine if the child received other treatment or experienced illness over the past month of study implementation. On day 0 and day 28, they will also be processed to ascertain low density parasitaemia estimates through quantitative polymerase chain reaction (qPCR).
Figure 2 below depicts the planned sample collection time points and subsequent sample processing sequence). We aim to recruit participants from Nakapiripit, one of the two research districts.

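### The abstract promises a DP–SPAQ safety comparison at 3–59 months, but the components described allow one only from 6 months, without stated randomisation, and contradict each other on day 2

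*Protocol article*

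**What the plan says.** **The comparative aim.** The abstract's Objective includes the "safety and tolerability of DP compared to that of SPAQ among 3-59 months old children".

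**Age by drug.** Under Aims and objectives, objective 1 sets 3–59 months for SPAQ and 6–59 months for DP. Table 1 describes objective 2a (1,250 children) as "Chemoprevention efficacy cohort study – children under 3–59 months for SPAQ and 6-59 months for DP".

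**Objective 2b.** The aim is "to assess the safety of DP in children 3–6 months through pharmacometric analysis". Table 1 gives it 30 children under the label "Safety of DP in 3–6 month old children through pharmacometrics to low dose DP". The abstract's Methods describe the same component as "a sub study examining pharmacokinetics of DP in children between 3 to <6 months", with no mention of safety. The Introduction says tolerability evidence for DP is lacking in very young children, because earlier safety studies mostly enrolled children above 6 months.

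**The cohort.** Under Recruitment and data collection, children are "referred to a designated study clinic for further assessment and non-randomized recruitment". Dosing is directly observed over the first three days of one cycle of either drug. Smears are taken together with "dry blood spots (DBS) taken at day 0, 2, 7, 14, 21 and 28". The clinician then asks whether the child had other treatment or "experienced any problem during all the scheduled sample collection days (Day 0, 7, 14, 21, 28").

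**Other components.** The cluster trial is described as recording malaria cases by passive surveillance. Data management lists the efficacy and safety studies separately from it. Study status says data collection is complete.

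**The concern.** A comparative safety statement needs children on both drugs in the same age range, and problems recorded in the same way for both. As described, no component gives this below 6 months, yet the abstract's claim starts at 3 months. From 6 months the comparison would rest on a cohort that is not described as randomised.

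Two further points bear on what can be claimed. The cohort text disagrees with itself about the visit that ends dosing, when acute intolerance is most directly observed. Objective 2b is called a safety assessment in one place and a pharmacokinetic study in another. It covers the age group for which the article itself says evidence is thin, so an event-free 30 could be over-read. The study is meant to inform malaria policy, so the reach of its safety statement matters.

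**Working it through.** **1. The plan's own total.** Table 1 rows sum to 4,270 + 1,250 + 30 + 1,500 + 144 = 7,194, as stated. No derivation is given for 30 or 1,250, so neither can be reproduced. The split of the 1,250 by drug is not stated.

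**2. Who can be compared, by age.**

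| Age | DP children described | SPAQ children described | Problems asked about in both? |
|---|---|---|---|
| 3 to <6 months | 30 in objective 2b | Cohort and trial, but no group in 2b | No shared component |
| 6–59 months | Cohort and trial | Cohort and trial | Cohort only, as described |

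The 3–59 month contrast is thus available only from 6 months.

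**3. Size of the age imbalance.** The range 3–59 months spans 57 monthly ages, of which three (3, 4 and 5) lie below 6 months. If ages were evenly spread (an assumption), 3/57 = 5.3% of SPAQ children would have no DP counterpart. An unrestricted contrast would then shift by 0.053 × the difference in event rate between younger and older SPAQ children, or about 0.5 percentage points for each 10-point difference. The numerical shift is modest. The larger matter is a claim about an age group with no comparison. Restriction also costs few children.

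**4. What 30 children support** (exact binomial).
- Zero events: two-sided 95% upper limit = 1 − 0.025^(1/30) = 11.6%; one-sided = 1 − 0.05^(1/30) = 9.5%.
- Three events in 30: 95% CI 2.1% to 26.5%.
- Probability of at least one event = 1 − (1 − p)^30, for assumed true rates p:

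| p | 1% | 2% | 5% | 10% |
|---|---|---|---|---|
| P(≥1 event) | 26% | 45% | 79% | 96% |

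- A 2% event would be missed entirely with probability 0.98^30 = 55%.
- A 95% chance of seeing one 1% event needs ln 0.05 / ln 0.99 = 298.07, that is 299 children.

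**5. Is the cohort simply too small?** Power at two-sided 5% with 1,250 children. Rates and splits are assumed, and the smaller group has the lower rate.

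| Rates | 1:1 split | 30:70 split |
|---|---|---|
| 5% vs 10% | 92% | 86% |
| 10% vs 15% | 76% | 67% |
| 1% vs 3% | 72% | 58% |
| 1% vs 2% | 31% | 21% |

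For common reactions the limiting factor is comparability more than size.

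**6. The day lists.** Sampling days are 0, 2, 7, 14, 21 and 28. Problem-assessment days are 0, 7, 14, 21 and 28, although the sentence says this covers every scheduled sampling day. Day 2 is in the first list and absent from the second, so both cannot be right.

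**The case against.** **Age.** Table 1's row for the cluster trial gives 3–59 months for DP and SPAQ together, and Table 2 gives one range for all, so the abstract may only be describing the overall population. This does not rescue the comparison: objective 1 separates the ages by drug, and so does the Table 1 row for the cohort.

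**Location of the comparison.** No sentence says that the DP–SPAQ safety contrast is made in the cohort. That is an inference from what the article describes, and a condensed article may leave safety capture elsewhere to the full protocol. This stands. The absence of adverse-event definitions or a safety analysis is therefore not held against the plan.

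**Confounding.** A reader might infer that the drug comparison is confounded. The documents do not show that. The word non-randomised qualifies recruitment, and how drug was allocated is not described.

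**Day 2.** A reader might also infer that day 2 was skipped and that the first assessment after dosing began was recall at day 7. That is not established. The child is seen for observed dosing and sampling, the sentence claims to cover all sampling days, and a day-28 survey asks about illness over the month. A dropped number is plausible, and Figure 2, which is not reproduced in the text, may settle it.

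**Objective 2b.** It is too strong to say that 30 children cannot inform safety. Assessment through exposure is legitimate, the objective names that route, and reactions at 10% or more would very likely be seen. The plan nowhere claims that 30 children exclude an event rate. What remains is that they cannot address uncommon reactions or a comparison with SPAQ, and that the two descriptions of 2b should agree.

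**Conclusion.** The concern holds in limited form. The 3–59 month comparative safety aim conflicts with the plan's own age ranges: no described component contrasts DP with SPAQ below 6 months. From 6 months a comparison is possible in the cohort, but it must be read as non-randomised unless allocation is shown to have been random. An unrestricted contrast would be unbalanced by age, with about 5% of SPAQ children unmatched if ages are evenly spread. For 2b, zero events in 30 leaves rates up to 11.6% unexcluded. The day-2 contradiction is certain as text; its effect on the data is unknown.

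The conclusion rests on the components as the article describes them. If the full protocol gives random drug allocation in the cohort, a SPAQ group at 3 to <6 months, or safety capture in the cluster trial, the corresponding part falls away.

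**What to change.** Data collection is complete, so the changes concern analysis, wording and reporting.

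1. Restate the comparative safety and tolerability aim as 6–59 months, in the abstract and wherever it is reported.
2. Analyse DP–SPAQ tolerability in that common age range, adjusted for age and other baseline items already collected, such as day-0 parasitaemia and bed-net use. State how drug was allocated, and label the comparison non-randomised unless allocation was random.
3. Describe 2b consistently with the abstract's Methods, as pharmacokinetic and exposure characterisation at 3 to <6 months. Report adverse events descriptively with exact 95% confidence intervals.
4. Reconcile the two day lists and report whether problems were recorded on day 2. If they were not, present early tolerability as day-7 recall.

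The cost is a few sentences, one restricted and adjusted analysis, the loss of the youngest SPAQ children from the comparison, and a more modest safety claim.
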